Although supervised center-based exercise interventions (herein referred to as supervised exercise for simplicity) are commonly prescribed to older adults, on some occasions feasibility can be limited by economic constraints, convenience, and access or time commitments [17, 18]. Under this context, unsupervised home-based exercise programs (herein referred to as unsupervised exercise) emerge as a potential alternative, and indeed different meta-analyses have shown that, compared with no exercise, unsupervised exercise can be effective for improving components of health and fitness in older adults [19, 20]. However, to date, there is no consensus on whether unsupervised exercise programs can be as effective –or even more cost-effective– than supervised ones. Some studies have shown greater benefits on different health variables with professionally supervised exercise programs compared to those performed autonomously at home [21–23]. On the other hand, other studies indicate that unsupervised exercise programs can be as effective as supervised ones [24–26]. For instance, Fisher et al. [27] found that supervised resistance exercise induces slightly greater muscle strength gains compared to unsupervised exercise in teenagers and adults, with minimal to no extra benefits on body composition. If their safety and cost-effectiveness are confirmed, unsupervised exercise programs would represent an alternative for increasing the accessibility of exercise for older adults, which would be of relevance for future public health policies. Nonetheless, most studies comparing supervised and unsupervised exercise have applied different interventions in each group (*e.g.,* different training types, duration, intensity, and exercise selection) [21]. Additionally, groups are often labeled as ‘supervised’ despite including some unsupervised sessions, and vice versa [28]. Therefore, well-designed randomized controlled trials (RCTs) that equalize exercise dose (*i.e.,* type, frequency, intensity, and volume) between both groups are warranted to draw definite conclusions on the role of supervision on the effectiveness of exercise programs.

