One of the factors that could moderate the effectiveness of exercise programs is adherence. In this regard, a recent meta-analysis by our research group showed that adherence to unsupervised exercise programs is usually low [29], probably due to a lack of motivation. Applying motivational strategies might help increase adherence to exercise programs, which could eventually result in greater training-induced adaptations [30–32]. Some studies have analyzed the impact of motivational strategies during exercise programs in older adults [33, 34]. However, these studies analyzed the influence of motivational strategies in supervised or unsupervised exercise interventions separately, but never before have they been examined in a single study.

The Promoting Training Programs for Health (PRO-Training) trial aims to cover all the abovementioned research gaps. The main goal of this RCT will be to determine the impact of supervision and motivational strategies on the safety, adherence, efficacy, and cost-effectiveness of different exercise programs for improving physical and mental health in older people.

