### Sample size

The sample size was determined by a priori power analysis using G ∗ Power 3.1.9.4 software. Input parameters were entered considering repeated measures ANOVA (group by time interaction), setting the probability of α error at 0.05, 1-β = 0.80, and 5 groups. The standardized mean difference used for calculations was 0.43, based on the effect of home-based exercise on lower-body muscle power in older adults reported in a previous meta-analysis [19]. The model indicated a total sample size of 100 individuals, and considering a dropout rate of 20%, we finally decided to enroll 120 participants.

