### Statistical analysis

Data will be preferentially presented as mean ± standard deviation or as proportions for continuous and categorical variables, respectively. Data normality will be assessed by the Kolmogorov–Smirnov test and will be log-transformed in case of non-normal distribution. Baseline differences will be assessed through a one-way ANOVA. A two-way mixed ANCOVA (group [*i.e.*, CON, SUP, SUP + , UNSUP, and UNSUP +] x time [*i.e.,* baseline, mid, post-intervention, and follow-up assessments]) will be performed, adjusting for baseline values as well as for any other sociodemographic/descriptive variables that may differ between groups (*e.g.,* age, sex). Subsequent post-hoc tests will be conducted to determine which groups significantly differ. Effect sizes will be calculated to assess the magnitude of the differences [87]. Falls and fall-related injuries will be presented as rates/person (ITT analysis) and rates/person/year (± 30 days; PP analysis), and as numbers. Adverse events and dropouts will be compared between groups through Chi-squared tests. Differences in adherence rates will be analyzed using an ANOVA test. Correlation analyses will be used to assess associations between motivators, barriers, and adherence to exercise sessions. Whenever possible, statistical analyses will be performed on an intention-to-treat (ITT) basis (including all randomized participants). The potential effects of missing values and dropouts will also be explored using multiple imputation and sensitivity analyses [88]. As recommended, a complementary per protocol (PP) analysis will be performed (*i.e.,* including only those participants with valid data for baseline and post-intervention assessments and an adherence to exercise program of at least 80%) [89]. SPSS version 24.0 (IBM Corp., Armonk, NY) will be used for statistical analysis, and the significance level will be set at p ≤ 0.05 for all tests.

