## Discussion

The main objective of the present trial is to examine the role of supervision and motivational strategies on the safety, adherence, efficacy, and cost-effectiveness of 4 different exercise programs for improving physical and mental health among people between 60 and 75 years old. We hypothesize that all exercise programs will be safe, and those that add cognitive-behavioral and motivational strategies will result in greater adherence and efficacy. Furthermore, we expect that UNSUP + will be the most cost-effective option, thereby increasing the accessibility of exercise to all older adults and consequently improving their health and quality of life.

As recommended by the World Health Organization, older adults should perform 150–300 min/week of moderate-intensity aerobic physical activity, 75–150 min/week of vigorous-intensity aerobic physical activity, or a combination thereof, as well as multicomponent physical activity focusing on functional balance and resistance training (≥ 3 days per week) [90]. The benefits of multicomponent exercise for mental and physical health are widely known [91–94]. Regular exercise helps in the prevention and management of different chronic diseases (*e.g.*, diabetes, obesity or overweight, hypertension, osteoporosis, or osteopenia) [95–98], thus leading to reduced attendance to medical consultations. According to Santos et al. [99], the global cost of inaction on physical inactivity would cost healthcare systems approximately 47.6 billion $ per year. If we add to this the low participation of older adults in physical activity, which decreases with age, we justify the need for safe and effective exercise programs for this population [16, 100].

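### The stated efficacy analysis tests supervision and motivation only piecemeal, between single arms; neither factor has a prespecified or powered test, and the 80% power belongs to the five-group omnibus interaction

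*Protocol article*

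**What the plan says.** The Background section gives the main goal as to "determine the impact of supervision and motivational strategies on the safety, adherence, efficacy, and cost-effectiveness of different exercise programs". The Discussion restates it and predicts that, among the exercise programs, "those that add cognitive-behavioral and motivational strategies will result in greater adherence and efficacy".

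Study design and Trial groups define a control arm and four exercise arms: supervised or unsupervised, each with or without the motivational programme. Each + arm gets the same exercise programme as its counterpart, and the two + arms get equivalent motivational strategies. The exercise arms are therefore the four cells of a 2x2, although the article calls the design parallel and does not use the word factorial.

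Statistical analysis specifies "A two-way mixed ANCOVA (group [*i.e.*, CON, SUP, SUP + , UNSUP, and UNSUP +] x time", that is, group as one five-level factor crossed with four visits. The follow-up step reads: "Subsequent post-hoc tests will be conducted to determine which groups significantly differ". No supervision effect, motivation effect, interaction between them or planned contrast is named. For adherence: "Differences in adherence rates will be analyzed using an ANOVA test", with no factors given.

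Sample size states: "Input parameters were entered considering repeated measures ANOVA (group by time interaction"), with alpha 0.05, power 0.80 and five groups. It adds: "The standardized mean difference used for calculations was 0.43, based on the effect of home-based exercise on lower-body muscle power in older adults", citing source 19. Background cites that source for the finding that, "compared with no exercise, unsupervised exercise can be effective for improving components of health and fitness in older adults [19, 20"]. The result was 100 participants, raised to 120 for 20% dropout.

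**The concern.** The question concerns two factors, whereas the stated test asks whether any of five arms follows a different course over time. A significant answer can come entirely from the control arm and then says nothing about supervision or motivation. A reader who sees 80% power may assume that it covers the two main questions. It covers neither: it belongs to the omnibus test, and its effect size appears to describe exercise against no exercise.

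The step that does bear on the factors is an unspecified set of comparisons between arms of about 20. A null result there would be hard to interpret. A positive one, picked from ten possible pairs after the data are seen, would be open to the charge of selection.

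**Working it through.** **Inputs.** From the article: SMD 0.43, alpha 0.05, five groups, 100 evaluable and 120 enrolled, four visits. Assumed because not stated: equal allocation (100/5 = 20 completers per arm), two-sided pairwise tests, and correlation rho between baseline and outcome of 0, 0.5, 0.7 or 0.8.

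**1. The plan's own figure.** For the group by time interaction in repeated measures ANOVA, lambda = f²·N·m/(1 − rho), df1 = (k − 1)(m − 1), df2 = (N − k)(m − 1). Take f = 0.43/2 = 0.215, k = 5, m = 4, rho = 0, N = 100. Then lambda = 0.046225 × 100 × 4 = 18.49, df = 12 and 285, and power is 0.814. The smallest N reaching 80% is 98, or 100 in equal groups. The stated 100 is thus reproduced as a sample size for the omnibus interaction. It needs a particular correlation entry: rho = 0.5 with four measurements would give 55.

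**2. What the omnibus test responds to.** Simulation with 100 completers, correlation 0.7 between visits and effects of 0, 0.7, 1 and 0.5 times the full value over the four visits (all assumed):
- All exercise arms 0.8 SD better than control, neither factor having any effect: group by time significant in about 80% of runs.
- A motivation effect of 0.43 and nothing else: significant in about 38%.

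**3. One pairwise test.** Noncentrality = [0.43/√(1 − rho²)]·√(n/2), where 1 − rho² is the residual variance after baseline adjustment. With n = 20 and rho = 0 this is 0.43 × √10 = 1.36 on 38 df (critical value 2.02).

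**4. A pooled factor contrast.** The same formula with n = 40 per side: 0.43 × √20 = 1.92 at rho = 0. This assumes the full 0.43 at both levels of the other factor.

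| rho | one pair, 20 vs 20 | same, Bonferroni over 10 pairs | pooled, 40 vs 40 | pooled, alpha 0.025 per factor |
|---|---|---|---|---|
| 0 | 26% | 7% | 48% | 36% |
| 0.5 | 33% | 9% | 59% | 48% |
| 0.7 | 46% | 16% | 76% | 66% |
| 0.8 | 60% | 26% | 89% | 82% |

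With no dropout (24 per arm), the unadjusted pairwise figures are 31, 39, 53 and 68%. With 120 less 20% (96, or 19.2 per arm), they are 25, 32, 44 and 58%. At 80% power one pair needs about 85, 64 or 44 per arm for rho 0, 0.5 or 0.7.

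**5. When pooling does not help.** Suppose motivation adds 0.43 in the unsupervised arms and nothing in the supervised arms. The pooled difference is (0.43 + 0)/2 = 0.215, with noncentrality 0.215 × √20 = 0.96 at rho = 0. Power is 16% at rho = 0 and 26% at rho = 0.7, against 26% and 46% for UNSUP+ versus UNSUP. The interaction test for a difference of 0.43 has noncentrality 0.43/√(4/20) = 0.96, hence the same 16% and 26%.

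**The case against.** A reader might infer that the plan never tests supervision or motivation at all. The article does not support that. Post-hoc tests between groups would include SUP versus UNSUP, SUP+ versus UNSUP+, SUP versus SUP+ and UNSUP versus UNSUP+, which are the simple effects of the two factors.

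A reader might also conclude that pooled contrasts should replace those comparisons. That is unsound. The Abstract asks whether motivation can enhance unsupervised exercise in particular, Background places the adherence problem in unsupervised programmes, and the Discussion singles out UNSUP+ as the expected most cost-effective arm. All of this makes an interaction plausible, and step 5 shows that pooling would then do worse. Arm-level comparison is a legitimate part of this trial.

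The power figures have limits. They borrow 0.43 as the size of a supervision or motivation effect, although its source appears to concern exercise against none, so differences between active arms may be smaller. The correlation is assumed. The figures describe a continuous outcome such as leg-press power, and show nothing about power for safety, adherence or costs.

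Naming post-hoc contrasts and the multiplicity method is commonly left to an analysis plan, and the adherence ANOVA is too briefly described to exclude a factorial form. Silence on those details is not the point here. What remains is that the article does state its efficacy model, its follow-up step and its power basis, and none of the three is aimed at the factors named in its objective.

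**Conclusion.** The concern holds in this form: the stated efficacy analysis addresses supervision and motivation only through single-arm comparisons, and it neither prespecifies nor powers a test of either factor. The stated 80% belongs to the omnibus interaction.

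Under the assumptions above, power for one pairwise test at 0.43 is 26 to 60% over correlations 0 to 0.8, and lower with any multiplicity adjustment. A pooled contrast raises it to 48 to 89% if the effect is the same at both levels of the other factor. Pooling is a large gain but not a full cure: with 100 completers it stays below 80% at correlations up to 0.7, and it loses its advantage if the effect is confined to one level.

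**What to change.** Add to the planned model, without removing the arm-level comparisons, four prespecified contrasts:

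1. Supervision: SUP and SUP+ against UNSUP and UNSUP+.
2. Motivation: SUP+ and UNSUP+ against SUP and UNSUP.
3. The supervision by motivation interaction, reported with its confidence interval.
4. The four exercise arms against CON.

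Apply the first three to adherence as well, where CON plays no part. Name the simple effects to be kept as follow-up comparisons, for example UNSUP+ versus UNSUP, and state how alpha is handled across the whole set. In Sample size, say that 80% refers to the omnibus group by time interaction, and give the power of the pooled contrasts with the correlation and effect size assumed.

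The cost is wording in the analysis plan, fixed before unblinding, with no extra participants or data. The downside is that each pooled effect averages over the other factor and the interaction test is too weak to warn reliably when that misleads, so the simple effects must be reported beside it.

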### Trial groups

All participants allocated to exercise intervention groups will complete a 24-week multicomponent exercise program consisting mostly of resistance exercises (3 sessions per week; 60 min per session). The exercise program will be reported following the Consensus on Exercise Reporting Template (CERT) [38] (see Supplementary Table 2). After completing the baseline assessment, participants will be randomly allocated to the 5 study groups. After randomization and irrespective of intervention group allocation, a member research team member will inform the participant about the intervention and assessment plan.

The exercise program for all intervention groups will be divided into 3 difficulty levels, increasing every 8 weeks. Each will include 3 sessions comprising of warm-up, balance, resistance, aerobic, and flexibility exercises (Tables 1 and 2). Further information about the training variables is available in Supplementary Table 3.

**Table 1 Tab1:** Supervised exercise program

	**Session nº**	**Exercise nº**	**Intensity report**	**LEVEL 1**	**LEVEL 2**	**LEVEL 3**	**Type**
WARM-UP	1, 2 & 3	1	-	Seated ankle circumduction			Joint mobility
		2	-	Knee flexo-extension			
		3	-	Hip circumduction			
		4	-	Forward–backward shoulder circumduction			
		5	-	Wrist circumduction			
		6	-	Neck mobility			
		7	-	Diagonal foot touches	Foot touches forward, to the side and back with hands on the waist	Foot touches forward, to the side and back with arms in cross position	Balance
		8	-	Heel lifts	One leg balance	One leg balance with arms in cross position	
		9	-	Lateral movement without impact	Lateral movement with impact	Rope skipping	Soft cardio
		10	-	´V´ front	Knee-elbow	Low skipping	
MAIN ACTIVITY	1	1	-	One leg balance with arms in cross position	One leg balance with leg abduction	One leg balance with shoulder flexion	Balance
		2	RIR	Machine chest press	Cable crossover	Dumbbell chest press	UB push (pectoral, triceps)
		3	RIR	Box squat	Goblet squat	Jump squat	LB (quadriceps, gluteus)
		4	RIR	Pulley shoulder flys	Alternating dumbbells shoulder flys	Simultaneous dumbbells shoulder flys	UB pull (trapezius, deltoid)
		5	RIR	Assisted TRX lunge	Lunge	Weighted lunge	LB (quadriceps, gluteus)
		6	RPE	Front plank with shoulder touches	Front plank with knees	Front plank	Core
		7	RIR	Seated rowing machine	Standing cable row (medium height)	Unilateral dumbbell row	UB pull (dorsal)
		8	RIR	Knee-banded seated hip abduction	Monster walk	Clamshell	LB (gluteus)

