### Outcome measures

#### Primary outcomes

##### Safety

The number of falls and adverse events will be recorded. Participants in the CON, UNSUP, and UNSUP + groups will record their falls and adverse events during and outside exercise sessions with a diary [39, 40]. In the SUP and SUP + groups, the sports scientist will register the incidence of falls and adverse events during exercise sessions, and participants will register them outside the exercise sessions using a diary.

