##### Adherence to the program

Adherence to the program will be calculated as a ratio between the sessions completed from those initially prescribed ([sessions completed/total sessions expected] × 100), where 0% indicates total non-adherence and 100% indicates full adherence [40]. The sports scientist will record adherence to the exercise program in the SUP and SUP + groups [41], while in the UNSUP and UNSUP + groups, it will be automatically registered through the mobile app [42].

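### The only person-year fall rate is tied to the per-protocol set, which drops participants whose fall stopped training, and the ITT fall rate has no time denominator

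*Protocol article*

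**What the plan says.** The Statistical analysis section fixes both the measures and their analysis sets: "Falls and fall-related injuries will be presented as rates/person (ITT analysis) and rates/person/year". The sentence goes on to assign the per-year version to the PP analysis and to add raw numbers. The section defines PP as "including only those participants with valid data for baseline and post-intervention assessments", together with "an adherence to exercise program of at least 80" per cent. Under Adherence to the program, adherence is the ratio "sessions completed/total sessions expected] × 100", with no stated exemption for sessions lost through injury. Trial groups sets 24 weeks at three sessions per week for the exercise arms; the control group (CON) has no programme.

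The same section makes ITT in all randomised participants the default where possible, calls PP complementary, and plans multiple imputation and sensitivity analyses for missing data and dropout. It also states: "Adverse events and dropouts will be compared between groups through Chi-squared tests". Data collection and management says that data from people who withdraw are kept and analysed. Sample size allows for 20% dropout. The eligibility section foresees stopping the intervention when a health problem affects the capacity to exercise.

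**The concern.** A rate per person-year is the natural way to compare falls when follow-up varies, and 20% planned dropout means that it will vary. The article computes this rate only in people who completed most of the training and came to the post-intervention assessment. A fall that stops training can cause failure on either condition, so the filter selects on something that the harm itself can bring about. The ITT rate avoids that selection but counts persons and not time, so it does not correct for unequal follow-up. No planned fall rate does both. The trial hypothesises that all its exercise programmes are safe, and a person-year rate that can lose the most disabling falls is a poor basis for judging that.

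**Working it through.** The article gives no fall rate, event count or safety power, so there is no planned figure to reproduce.

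**1. The PP cut-off.**
- Prescribed sessions: 24 × 3 = 72 (Trial groups).
- Threshold: 0.80 × 72 = 57.6, so 58 sessions are needed.
- Sessions that may be missed: 72 − 58 = 14, or 14 / 3 = 4.7 weeks of training.
- Missing 15 gives 57 / 72 = 79.2%, which is excluded.

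A participant with otherwise perfect attendance leaves PP when a fall costs 15 or more sessions; someone who has already missed sessions leaves after a smaller loss. A fall after session 58 (58 / 3 = week 19.3) does not remove a full attender who has post-intervention data.

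**2. CON.** Expected sessions are zero, so the adherence ratio is undefined. If the condition is applied literally, no CON participant can meet it. If it is waived, CON is filtered only on post-intervention data, while the exercise arms are also filtered on adherence.

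**3. How far the PP rate can move.** In a simulation of Poisson falls over 24 weeks (400,000 per arm), the comparator was treated as CON: no adherence filter, and falls that never end follow-up. The exercise arm had twice the fall rate, with full attendance until a fall stopped training. Comparator rates of 0.3, 0.5 and 1.0 per person-year were tried; the ranges below cover all three. Every input here is an assumption.

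| Chance that a fall stops training | PP person-year ratio, injured stay in follow-up | PP person-year ratio, injured withdraw |
|---|---|---|
| 0.3 | 1.52 to 1.53 | 1.39 to 1.40 |
| 0.6 | 1.03 to 1.04 | 0.79 to 0.80 |
| 0.9 | 0.56 | 0.20 |

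The true ratio is 2.0 throughout. The ITT per-person ratio was 1.98 to 2.01 when injured participants stayed and 1.36 to 1.92 when they withdrew. The ITT person-year ratio was 1.98 to 2.01 in every scenario.

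**4. Dilution of the ITT per-person rate.** If a fraction d leaves uniformly over the period, leavers contribute half of it on average, so mean exposure is 1 − d/2. With equal true rates, the apparent ratio is the ratio of exposures. The dropout splits are assumptions.
- 30% versus 10%: 0.85 / 0.95 = 0.89.
- 25% versus 15%: 0.875 / 0.925 = 0.95.
- 20% versus 20%: 0.90 / 0.90 = 1.00.

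**The case against.** The strongest reply is that harm is not hidden. ITT is the default and PP only complementary; the ITT rate and the raw numbers keep every recorded fall; data from withdrawn participants are retained; dropout is compared between groups, so unequal loss would be seen; and sensitivity analyses are planned. All of this stands. A reader might infer that a harmful arm could pass as safe across the whole report. The documents do not support that. In the simulation the ITT per-person ratio was diluted but never reversed. Reversal appeared only in the PP rate, and only when well over half of falls ended training, a proportion for which the article gives no basis.

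A reader might also infer that the plan favours the unsupervised arms because the Background expects little adherence there. The Background speaks of adherence, not of lost follow-up. Someone who skips sessions can still keep the falls diary, and Sample size gives one overall dropout figure.

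Two neighbouring matters are secondary. The chi-squared comparison of adverse events also ignores follow-up time. In the supervised arms "the sports scientist will register the incidence of falls and adverse events during exercise sessions", while unsupervised participants record their own. Neither is needed for this point.

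It may be said that an article can leave rate models to a fuller plan. That is true of the model, but this article itself assigns each fall rate to an analysis set, and that assignment is the problem.

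**Conclusion.** The point holds in a limited form. The person-year fall rate is restricted to a set that a disabling fall can remove a participant from, and the filter cannot work in CON as it does in the exercise arms. That rate can understate falls in the exercise arms, by an amount that depends on how often falls stop training, which is unknown. The ITT per-person rate and counts are sound as counts and suffer only if follow-up is shortened unequally: none at equal dropout, about 5% at 25% versus 15%, and about 11% at 30% versus 10%, under uniform dropout. The direction between arms cannot be stated from the documents. This is an inexpensive correction to a primary outcome; it does not show that the safety analysis as a whole would mislead.

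**What to change.** Make the main fall measure the number of falls, and of fall-related injuries, per person-year of observed follow-up in all randomised participants by allocated arm. A Poisson or negative binomial model with a log follow-up time offset would serve. Keep the ITT per-person rate and the counts beside it. Keep the PP rate only as a labelled supplementary figure that is not used to support the safety conclusion, and state how PP is defined for CON.

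The cost is analysis wording and a follow-up time for each participant up to the last diary or contact date. It needs no additional participants or visits and no change to the diaries during recruitment. The downside is wide intervals if falls are few.

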### Participant inclusion and exclusion criteria

The inclusion criteria will be the following: (1) individuals aged 60 to 75 years old; (2) fluency in Spanish language (both written and spoken); (3) ability to walk independently; (4) physical capability to engage in an exercise program; (5) competence in using a smartphone and mobile applications without assistance.

Participants meeting any of the following criteria will be excluded from the study: (1) individuals with a history of acute or terminal illness, as well as those who have experienced myocardial infarction, coronary artery bypass grafting, angioplasty, angina, or other cardiac conditions within the past year; (2) uncontrolled medical problems that the physician believes would preclude them from participating in an exercise program, such as acute systemic illness (*e.g.,* pneumonia), acute rheumatoid arthritis, and acute or unstable heart failure; (3) conditions requiring a specialized exercise program such as uncontrolled epilepsy, significant neurological disease or impairment, inability to maintain an upright seated position or unable to move independently, multiple sclerosis, cancer, Parkinson’s, Alzheimer’s, or chronic obstructive pulmonary disease; (4) uncontrolled hypertension diagnosed by a physician; (5) type I diabetes or uncontrolled type II diabetes; (6) history of major psychiatric illness (*e.g.,* schizophrenia, generalized anxiety disorder, or depression according to the DSM-5); (7) morbid obesity (body mass index > 39.9); (8) having experienced three or more self-reported falls in the last year; (9) not living in the community (i.*e.,* residing in nursing homes); (10) participation in an exercise program within the preceding six months; (11) having been diagnosed with COVID-19 with hospitalization in intensive care unit; (12) any other condition that could interfere with the study purposes and pose a risk to the participant, as determined by the researcher and physician. Eligibility criteria will be verified by a physician and a member of the research team during telephone screening and in the initial assessment. A medical history and the PAR-Q (Physical Activity Readiness Questionnaire) will be administered at the initial assessment.

Criteria for discontinuing intervention for a given trial participant include participant request, disease onset or worsening impairing research results or affecting exercise capacity, etc.

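### The only fall and injury rate per unit of time is planned in the per-protocol set, which can exclude people because of the event being counted; this probably, though not certainly, favours exercise

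*Protocol article*

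**What the plan says.** Safety, recorded as falls and adverse events, is a primary outcome (Primary outcomes, Safety). For its analysis, the Statistical analysis section says: "Falls and fall-related injuries will be presented as rates/person (ITT analysis) and rates/person/year (± 30 days; PP analysis), and as numbers". So there are three displays, and the only one with time in the denominator belongs to the PP set.

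The same section defines that set as "including only those participants with valid data for baseline and post-intervention assessments and an adherence to exercise program of at least 80"%. It also makes ITT the default wherever possible and calls PP complementary.

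Other sections supply the rest:

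- Adherence to the program: adherence is completed sessions as a percentage of prescribed sessions. No allowance is stated for sessions missed through injury.
- Trial groups: exercise participants "will complete a 24-week multicomponent exercise program" with "3 sessions per week; 60 min per session". CON has no prescribed sessions.
- Participant inclusion and exclusion criteria: reasons for discontinuing the intervention include the participant's request and "disease onset or worsening impairing research results or affecting exercise capacity".
- Data collection and management: data from people who withdraw are kept and analysed.
- Discussion: the hypothesis is that all exercise programmes are safe.

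**The concern.** A fall or injury can cause non-adherence. A rate restricted to adherers then selects on a consequence of the outcome it measures: the injured person and the fall both leave the calculation. Only the exercise arms can lose people through the adherence rule, so a comparison of person-year rates with CON may be tilted towards the trial's own safety hypothesis.

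The ITT figure does not fill the gap. It is a rate per person, so a participant who withdraws early counts as one full person while contributing little time in which a fall could be recorded. For a primary safety outcome, the plan therefore has no time-based rate in all randomised participants.

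**Working it through.** **1. The threshold.** Inputs are 24 weeks and 3 sessions per week (Trial groups) and the 80% rule (Statistical analysis).

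- 24 × 3 = 72 sessions; 0.80 × 72 = 57.6, so 58 are needed.
- 57/72 = 79.2% is out; 58/72 = 80.6% is in. Missing 72 − 57 = 15 sessions excludes an otherwise fully attending participant.
- 58/3 = 19.3, so with full attendance session 58 falls in week 20.

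**2. Effect on the rate.** The article gives no fall rate, so there is no stated figure to reproduce. Let λ be the true rate over the 24 weeks and q the assumed probability that a fall ends training. Take falls as evenly spread and other non-adherence as unrelated to falling. Falls that do not stop training stay in. Falls that stop it stay in only if they occur in the last 14/72 of the programme. So:

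PP rate = λ[(1 − q) + q × 14/72] = λ(1 − q × 58/72)

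| q (assumed) | PP rate / true rate | Too low by |
|---|---|---|
| 0.10 | 0.919 | 8% |
| 0.25 | 0.799 | 20% |
| 0.50 | 0.597 | 40% |
| 1.00 (extreme) | 0.194 | 81% |

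λ cancels. A Poisson simulation at 0.3, 0.6 and 1.0 falls per person-year gives the same ratios (about 0.92, 0.80, 0.60 and 0.19). If true rates were equal and CON lost nobody through falls, these would also be the apparent exercise-to-CON rate ratios.

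**3. In events.** Assume 24 per arm (120/5, equal allocation), λ = 0.6 per person-year, q = 0.25 and 20% other non-adherence. Expected falls are 24 × 0.6 × 24/52 = 6.6. The simulation keeps about 76% of the arm in the PP set, at a rate of 0.48: 24 × 0.76 × 0.48 × 24/52 = 4.0 falls. The reported rate is 0.48 instead of 0.60.

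**4. Direction.** Suppose 30% are non-adherent for other reasons and fall at k times the adherers' rate. Then PP/ITT = (1 − q × 58/72)/(0.7 + 0.3k).

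| q | k = 0.7 | k = 0.5 |
|---|---|---|
| 0.10 | 0.919/0.91 = 1.01 | 0.919/0.85 = 1.08 |
| 0.25 | 0.799/0.91 = 0.88 | 0.799/0.85 = 0.94 |
| 0.50 | 0.597/0.91 = 0.66 | 0.597/0.85 = 0.70 |

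So the sign can reverse when few falls stop training and non-adherers fall less.

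**5. Counting period.** The article does not say when fall recording ends. If falls were counted to week 49, only stopping falls in the first 19.3 weeks would be lost, and the ratio becomes 1 − q × 19.3/49: 0.96 at q = 0.10 and 0.80 at q = 0.50. The understatement would then be about 4% to 20%.

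**6. The ITT rate per person.** Someone whose diary ends in week 3 supplies 3/24 = 12.5% of the programme period but counts as one person. With the 20% dropout used in Sample size, the recorded rate would be 0.8 + 0.2 × 0.5 = 0.90 of its full value if dropouts left halfway on average, and 0.8 + 0.2 × 0.125 = 0.825 if all left in week 3. The leaving times are assumptions.

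**The case against.** A reader might infer that safety as a whole is assessed only in adherers, or that injured participants vanish from the report. The documents do not support that. The same sentence promises ITT rates per person and raw numbers, and withdrawn participants' data are kept. Adverse events are compared by Chi-squared tests to which no PP restriction is attached. Falls are only to be presented; no PP test of falls is stated.

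Other parts of the defence also stand:

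- The direction of bias is not certain, as step 4 shows.
- A CON participant who is hurt and misses the post-intervention assessment is excluded too; only the adherence filter is one-sided.
- Stopping training is not leaving observation. Nothing says diaries end when training ends, so the weakness of the ITT rate concerns only people whose recording stops.
- The listed health reason for discontinuing concerns disease, not falls as such. A participant who pauses but still completes 58 sessions stays in.
- Numbers are small. With 6 falls in an arm, the exact Poisson 95% interval runs from roughly 2 to 13, so one lost fall is within noise.

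Three replies do not succeed. Multiple imputation and sensitivity analyses address missing values and dropouts; they do not restore people whom the adherence rule removes from the PP rate. Imprecision is no reason to accept an avoidable bias. And although an article may leave exposure definitions to a fuller plan, assigning the person-year rate to the PP set is a rule it states, not a detail it omits.

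**Conclusion.** The point holds in a limited form. The planned person-year rate of falls and fall-related injuries selects on adherence, which those events can themselves reduce, and the adherence filter acts on exercise arms only. The 58-of-72 cut follows from the plan. The size does not: the figure of about 8% to 40% too low assumes that 10% to 50% of falls end training, that falls are counted over the 24 weeks and that other non-adherence is unrelated to falling. A longer counting period shrinks it, and lower fall rates among other non-adherers can offset it.

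It would go too far to say that exercise arms will look safer than they are. That is the likely direction for one of three displays, and the other two retain the events. Because safety is a primary outcome and the plan itself prefers ITT, the analysis should still be changed.

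**What to change.** Make the main time-based rate falls and fall-related injuries per observed person-time in all randomised participants, analysed as randomised. Each person's time runs from randomisation to the end of diary recording or withdrawal; a Poisson or negative binomial model with log person-time as offset would serve. Keep the ITT rate per person and the raw numbers, and show the PP person-year rate only as a labelled supplementary table.

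The cost is a sentence of analysis text and a little extra analysis work. The date on which each participant's diary observation ends must be recorded; the article does not say that it is. The exercise-arm rates may look less favourable.
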